#### **9.1.1.2 Data analysis**

Differences in the infectivity rate before (Day 1/ Visit 1) and after vaccination (Month 7/ Visit 4) will be compared in cervical, anal, vulvar, urine and oral samples using non-parametric Wilcoxon signed rank test.

For cervical samples, joint and stratified analysis for HPV-RIFT1 and HPV-RIFT2 cohorts will be done.

Oral, vulvar, urine and anal samples included in the HPV-RIFT1 and HPV-RIFT2 cohorts will be analyzed together to obtain the minimal sample size established for this analysis. If sample size would allow stratified analysis for HPV-RIFT1 and HPV-RIFT2 cohorts, it will be performed and submitted.

Sensitivity analysis including only cases showing negative seroconversion before vaccination will be performed.

### **9.1.2 Secondary Objectives**

#### **9.1.2.1 Objective 2**

To summarize antibody responses to vaccination (for each of the 9vHPV-covered HPV types (6, 11, 16, 18, 31, 33, 45, 52, and 58)).

##### **9.1.2.1.1 Endpoints**

HPV 6/11/16/18/31/33/45/52/58 L1 antibody detection/titration using cLIA/ ELISA in serum samples collected before and after 9vHPV vaccination.

##### **9.1.2.1.2 Inclusion in the analysis population**

All cases showing positive seroconversion for HPV16/18/16+18 will be included.

For each HPV type analyzed, proportion of seroconverted cases after 3 vaccine doses (Month 7/ Visit 4) will be provided.

It is expected that 90% of cases show positive seroconversion after 3-dose 9vHPV vaccination.

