| 
2) Secondary Objective. To summarize antibody responses to vaccination (GMT and seroconversion percentages) for each of the 9vHPV-covered HPV types (6, 11, 16, 18, 31, 33, 45, 52, and 58)
 
Hypothesis. A higher level of anti-HPV antibodies is expected after 9vHPV vaccination than after a natural serological response to an HPV infection. Anti-HPV antibodies titration will allow to identify subjects with natural serological responses before vaccination.
 | 
 
● HPV 6/11/16/18/31/33/45/52/58 L1 antibody titration in serum samples collected before and after 9vHPV vaccination, using             
 
– ELISA for types 16 and 18 in samples from RIFT-HPV 1 and 2 study cohorts,
 
– cLIA for all 9vHPV-covered types in samples from RIFT-HPV 1 study cohort.
 
 
 
                                                                                                                                                                                                                                                                                                                                                                                                                                                                                                                                                                                                                                                                                                                   |

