### 9.1.4 Definitions Regarding Data Description and Analysis.

**Infectivity rate:** The infectivity rate of cervical, anal, urine, vulvar and oral samples collected from study subjects before and after 9vHPV vaccination will be obtained measuring the in-vitro expression of HPV biomarker E1E4 mRNA in HaCaT keratinocytes incubated during 24h with study samples (quantitative variable). The expression level of a positive control sample and the human gene HPRT1 will be used to normalize the expression measurements. The quantity of HPV-infected keratinocytes (i.e., expressing E1E4 mRNA) will be directly proportional to the quantity of free HPV viral particles present in samples (i.e. not neutralized by HPV antibodies). Reduction in infectivity will be expressed as the difference between the infectivity rate of cervical, anal, urine, vulvar and oral samples before and after the subject receives 9vHPV vaccination.

**HPV persistent infection:** an HPV infection of the same genotype and sample type (oral, anal, urine, vulvar or cervical) detected in samples collected at Day1/Visit 1 and Month 7/Visit 4 is defined as persistent infection (qualitative variable: persistent or non-persistent infection).

**HPV productive infection:** an HPV positive infection that produce new viral particles detected by immunoassays or EM in oral, anal, urine, vulvar or cervical samples is defined as productive infection (qualitative variable: presence or absence of viral particles).

**Positive/negative HPV seroconversion:** it is defined as the status of study serum samples regarding presence (positive) or absence (negative) of type-specific HPV antibodies. Positive seroconversion may occur after administration of study vaccine, or by subject's natural immunological response to a previous HPV infection. Negative seroconversion may occur when study vaccine fails to trigger an immunological response in the subject. Quantitative results of the HPV antibodies detection test are reported in terms of arbitrary units (milliMerck units/ml). Results may be reported qualitatively as positive or negative seroconversion for type-specific HPV antibodies.

**Anti-HPV antibodies exudation:** type-specific HPV antibodies will be detected in cervical, anal, urine, vulvar and oral samples (cLIA/ ELISA), and results will be expressed qualitatively as antibody presence or absence.

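### The secondary seroconversion analysis admits only women with positive seroconversion for HPV16/18, so its Month 7 percentages are biased upward, and its definition counts natural antibody present before vaccination

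*Protocol*

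**What the plan says.** Protocol section 3 gives the secondary objective: "To summarize antibody responses to vaccination (GMT and seroconversion percentages) for each of the 9vHPV-covered HPV types". Section 9.1.2.1.2 fixes the population: "All cases showing positive seroconversion for HPV16/18/16+18 will be included". It does not say at which visit this condition is judged. The same section then gives the statistic, "For each HPV type analyzed, proportion of seroconverted cases after 3 vaccine doses (Month 7/ Visit 4) will be provided", and the expectation, "It is expected that 90% of cases show positive seroconversion after 3-dose 9vHPV vaccination". No other denominator for the percentage appears in the protocol.

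On seroconversion, section 9.1.4 says "it is defined as the status of study serum samples regarding presence (positive) or absence (negative) of type-specific HPV antibodies", and adds: "Positive seroconversion may occur after administration of study vaccine, or by subject's natural immunological response to a previous HPV infection". Section 9.1.1.2 uses the word in the same sense when it plans, for the infectivity endpoint, "Sensitivity analysis including only cases showing negative seroconversion before vaccination will be performed". Seroconversion in this protocol therefore means serostatus at a visit, not a change from Visit 1.

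**The concern.** There are two separate faults.

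First, a woman who is antibody-negative for both type 16 and type 18 leaves the denominator of the proportion that should count her as a failure. Section 9.1.4 itself foresees vaccine non-response, and section 5.1 allows women with HIV, transplant immunosuppression or other immunosuppressive conditions to enrol, so failures are possible. Section 9.1.1.1.2 already removes women without positive seroconversion from the primary infectivity analysis, and section 9.1.2.2.1 carries that rule to the one-dose and two-dose analyses. The serology objective is where non-response would be expected to show, and its own population rule hides it.

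Second, because seroconversion is defined as antibody presence, a woman already seropositive from natural infection at Visit 1 is counted as seroconverted at Month 7. The hypothesis attached to this objective contrasts the vaccine response with the natural one, and section 2.2.4 says serology cannot tell the two apart in vaccinated HPV-positive individuals. Visit 1 status is the available means of separating them, and section 9.1.2.1.2 does not use it.

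**Working it through.** **Inputs.** From section 9.1.2.1.2: the inclusion condition, the per-type Month 7 proportion and the 90% expectation. From section 1.1.6: minimum enrolment of 39 and 30, so 39 + 30 = 69, used only for illustration and as if every woman had a Month 7 result for types 16 and 18. Not in the documents, and therefore assumed: the correlation between type 16 and type 18 failures, and baseline seropositivity.

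**The 90%.** The protocol states it without derivation, interval or sample size, so it cannot be reproduced. It is taken below as the true Month 7 rate.

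**1. Combined 16 and/or 18 result, inclusion judged at Month 7.** P(positive for 16 and/or 18, given inclusion for being positive for 16 and/or 18) = 1. Illustration with Clopper-Pearson 95% intervals:

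| | All women | Under the written rule |
|---|---|---|
| Both cohorts | 62/69 = 89.9% (80.2% to 95.8%) | 62/62 = 100% (94.2% to 100%) |
| RIFT-HPV 1 | 35/39 = 89.7% (75.8% to 97.1%) | 35/35 = 100% |
| RIFT-HPV 2 | 27/30 = 90.0% (73.5% to 97.9%) | 27/27 = 100% |

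**2. Single type, inclusion type-matched or requiring both types.** Every included woman is positive for the type by the inclusion rule, so the type 16 and type 18 proportions are each 100%.

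**3. Single type, inclusion by either type.** Restricted rate = r / P(positive for 16 and/or 18), with r = 0.90 for each type.
- Independent failures: 0.90 / (1 − 0.10²) = 0.90 / 0.99 = 90.9%.
- Failures in the same women: 0.90 / 0.90 = 100%.
- No woman failing both types: 0.90 / 1 = 90%, the only case without bias.

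The restricted rate is never below the true rate.

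**4. The other seven types.** With a true 90%, the restricted rate stays at 90% if failures are independent of 16/18 failure and reaches 100% if the same women fail. The GMTs are computed in the same restricted group and move upward to the extent that 16/18 non-responders also respond poorly.

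**5. Definition of seroconversion.** Let s be the share seropositive at Visit 1, assume all of them stay positive, and take 90% seropositive at Month 7 among all women (not the restricted group of steps 1 to 4). Conversion among baseline seronegatives = (0.90 − s) / (1 − s).
- s = 20%: 0.70 / 0.80 = 87.5%
- s = 40%: 0.50 / 0.60 = 83.3%
- s = 60%: 0.30 / 0.40 = 75.0%

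**The case against.** A reader might infer that the type 16 and type 18 results are 100% whatever the vaccine does, and that 90% can never be observed. The documents do not support that without qualification. Proportions are reported type by type, not for 16 and 18 combined. Elsewhere the 16/18/16+18 label denotes infection with 16, with 18, or with both; read that way, a woman positive only for type 18 stays in the type 16 denominator as a failure. The inclusion visit is also unstated, and since serostatus can be positive before vaccination, even a combined Month 7 figure is not strictly fixed. This stands, and it limits the 100% to the readings in steps 1 and 2. It does not rescue the rule: judging inclusion at Visit 1, for example, would keep only women who were already seropositive.

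The inclusion sentence may be a slip for HPV16/18-infected women, since the 90% expectation presupposes non-responders in the denominator. That is plausible, but it confirms that the section contradicts itself and needs correcting.

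Natural immunity is partly visible: serum is taken at Visit 1, section 8.2.2.3 defines Visit 1 serostatus for cLIA and IgG LIA, and the synopsis words the objective as levels before and after vaccination. It would therefore go too far to say that natural antibody is ignored. But the Month 7 percentage as defined does not separate it, and the baseline-seronegative analysis in section 9.1.1.2 covers infectivity only.

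Finally, the objective is descriptive, with no test, threshold or sample size attached. That limits the consequence. It does not make the reported percentage right, nor is the matter left to a separate plan: section 9 positively fixes both the population and the definition.

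**Conclusion.** The point holds. The serology population is selected on the outcome it reports, in conflict with the protocol's own 90% expectation. How far the percentages are inflated depends on the reading of the inclusion sentence: fully to 100% for a combined result at Month 7 or under a type-matched or both-types rule, and from 90% to between 90.9% and 100% for single types under an either-type rule, going from independent to coincident failures. The effect on the other seven types and on the GMTs is upward but depends on how far failures are shared, which the protocol does not tell us.

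The definition is a second, independent fault; it plays no part in producing the 100%. Its size (87.5%, 83.3% or 75% true conversion behind a 90% figure) rests on assumed baseline seropositivity of 20%, 40% or 60% and on persistence of antibody to Month 7. Infection with type 16 or 18 at entry does not by itself establish baseline serostatus, least of all for the other seven types.

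The primary analysis does not use this population rule. A named secondary result would nevertheless be biased upward and would hide non-responders, so the text should be corrected before analysis.

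**What to change.** In section 9.1.2.1.2, replace the inclusion sentence with all vaccinated women who have a valid Visit 4 serum result for the type, regardless of that result. For each type report:

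- Month 7 seropositivity and GMT in all of these women;
- seroconversion, meaning seronegative at Visit 1 and seropositive at Visit 4, with only women seronegative at Visit 1 for that type in the denominator.

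In section 9.1.4, use seropositive and seronegative for status at a single visit, and keep seroconversion for the change. State whether the 90% expectation refers to seropositivity or to seroconversion. The serostatus rule in section 8.2.2.3 covers cLIA and IgG LIA; an equivalent rule should apply to ELISA, the only antibody assay planned for RIFT-HPV 2.

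The cost is wording only: serum is already collected at Visits 1 and 4. The reported percentage may become less favourable.

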#### **9.1.2.2 Objective 3**

To demonstrate viral infectivity reduction in cervical, oral, urine, vulvar and anal samples from HPV 16/18/16+18-positive women before and after vaccination with 1-dose or 2-dose regimen of 9vHPV.

##### **9.1.2.2.1 Endpoints, inclusion in the analysis population and data analysis**

The same endpoint, analysis inclusion criteria and data analysis as in primary objective will be applied for cases showing 1-dose and 2-dose 9vHPV vaccination.

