| 
2) Secondary Objective. To determine HPV antibody levels before and after vaccination (GMT and seroconversion percentages) for each of the 9vHPV-covered HPV types (6, 11, 16, 18, 31, 33, 45, 52, and 58)
 
Hypothesis. A higher level of anti-HPV antibodies is expected after 9vHPV vaccination than after a natural serological response to an HPV infection. Anti-HPV antibodies titration will allow identifying subjects with natural serological responses before vaccination.
                          | 
HPV 6/11/16/18/31/33/45/52/58 L1 antibody titration in serum samples collected before and after 9vHPV vaccination, using
 
 
- ELISA for types 16 and 18 in samples from RIFT-HPV 1 and 2 study cohorts,
 
- cLIA for all 9vHPV-covered types in samples from RIFT-HPV1 study cohort.
 
                                                         |
| 
3) Tertiary/Exploratory Objective. To demonstrate viral infectivity reduction in cervical, oral, urine, vulvar and anal samples from HPV 16/18/16+18-positive women before and after vaccination with 1-dose or 2-dose regimen of 9vHPV.
 
Hypothesis. Since serological response after administration of 2 vaccine doses is not inferior to 3 doses, infectivity reduction in cervical, anal, urine, vulvar and oral samples are expected to be detected after 2 doses, and at least partially after one dose.
 | 
Same endpoints as in primary objective.
                                                                                                                                                                                                                                                                                                                                                                   |

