| 
3) Tertiary/ Exploratory Objective. To demonstrate viral infectivity reduction in cervical, oral, urine, vulvar and anal samples from HPV 16/18/16+18-positive
                                                                                                                                                                                                                                                                                                                      | 
 
● Same endpoints as in primary objective.
 
                                                                                                                                                                                                                                                                                                                                                                                                                                                                                                                                                                                                                                                                                                                                                                                                                                                                                                                                                                                                                                           |

|                                                                                                                                                                                                                                                                                                                                                                     |  |
|---------------------------------------------------------------------------------------------------------------------------------------------------------------------------------------------------------------------------------------------------------------------------------------------------------------------------------------------------------------------|--|

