### 9.1.3 General Considerations on Data Analysis.

Sensitivity analyses using information provided by the study questionnaire about sexual activity, immunological status, concomitant medication and other will be performed when necessary.

Significant difference in the infectivity rate will be accepted with a p-value <0.05.

A partial analysis after completing 50% of the planned recruitment and a global analysis at the end of the 7-month follow-up will be carried out.

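### The 1-dose/2-dose objective is exploratory in the objectives tables but secondary in section 9, where it gets the primary analysis at an unqualified p<0.05 and so an uncontrolled error rate

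*Protocol*

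**What the plan says.** Both objectives tables give the 1-dose/2-dose aim the lowest rank: "Tertiary/Exploratory Objective" in section 1.1.5 and "Tertiary/ Exploratory Objective" in section 3. Section 4.1 lists it with the antibody objective under one merged secondary-and-tertiary lead-in, without saying which is which. Section 9, which carries the title of a statistical analysis plan, has no tertiary or exploratory heading. There the aim is Objective 3 (9.1.2.2), under the 9.1.2 heading "Secondary Objectives".

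The aim is confirmatory in wording: "To demonstrate viral infectivity reduction in cervical, oral, urine, vulvar and anal samples from HPV 16/18/16+18-positive" women. The same verb is used in the two tables and in section 4.1.

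For the analysis, section 9.1.2.2.1 states "The same endpoint, analysis inclusion criteria and data analysis as in primary objective will be applied" to the 1-dose and 2-dose cases. The primary analysis in 9.1.1.2 is a Wilcoxon signed rank test of before against after in cervical, anal, vulvar, urine and oral samples. Cervical samples are also analysed jointly and by cohort. Section 9.1.3 adds one threshold, with no exception for Objective 3: "Significant difference in the infectivity rate will be accepted with a p-value <0.05".

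**The concern.** The rank of an objective decides what a significant result may be used for. Under the two tables, a p-value below 0.05 after one or two doses generates a hypothesis. Under section 9, the same p-value can be reported as a demonstrated reduced-dose effect.

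Section 9 does not make these tests wait for the 3-dose comparison and sets no order between two doses and one. A reduced-dose effect could therefore be reported as shown even if the 3-dose primary fails. The full title features samples taken after one, two and three doses, and section 4.2.1 expects the results to inform vaccination of adult women, so readers will look for this conclusion. The sample size in section 9.2 rests on the 3-dose comparison alone.

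**Working it through.** **Plan's own figure.** The protocol states no error rate for Objective 3, so there is none to reproduce. Its minimum sizes of 39 and 28 belong to the 3-dose comparisons.

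**Inputs**
- Sites: 5 (section 9.1.1.2).
- Dose levels: 2 (section 9.1.2.2.1).
- Threshold: p<0.05 per comparison (section 9.1.3), two-sided as in section 9.2. That is 0.025 in the direction of a reduction.
- Visits: Visit 2 against Visit 1 for one dose and Visit 3 against Visit 1 for two doses, because section 4.1 has samples taken before each dose. This reads the objective as covering all women at those visits (assumption).
- Correlations: none given (assumed below).

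**Step 1, number of tests.** 2 dose levels × 5 sites = 10.

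**Step 2, independence as a reference only**
- Either direction: 1 − 0.95^10 = 0.401.
- Reductions only: 1 − 0.975^10 = 0.224.

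These values cannot be reached, because both dose levels use the same Visit 1 sample.

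**Step 3, shared baseline.** Let the infectivity measure have equal variance s² at each visit and equal correlation r between visits. Each change from Visit 1 then has variance 2s²(1 − r). Two changes from the same Visit 1 value have covariance s²(1 − r). Their correlation is the ratio, 0.5, whatever r is.

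A multivariate normal simulation (400,000 draws, no effect at any dose or site) with correlation 0.5 between dose levels gives:

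| Assumed correlation between sites | At least one p<0.05, either direction | At least one false reduction |
|---|---|---|
| 0 | 0.378 | 0.207 |
| 0.3 | 0.353 | 0.181 |
| 0.5 | 0.310 | 0.157 |
| 0.7 | 0.257 | 0.129 |
| 0.9 | 0.178 | 0.090 |

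Raising the correlation between dose levels to 0.7 lowers the last row to 0.165 and 0.083.

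**Step 4, comparison with one test.** For false reductions, 0.090/0.025 = 3.6 and 0.207/0.025 = 8.3 times nominal. In either direction, 0.178/0.05 = 3.6 and 0.378/0.05 = 7.6 times nominal.

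**The case against.** Several points on the other side are sound.

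- **A false claim is not likely.** A reader might infer from ten unadjusted tests that a false 1- or 2-dose claim is more probable than not. It is not: a false claim here means a false reduction, and that stays at about 21% or below. A figure above one half (51%) needs 14 tests, found by adding the two cervical cohort strata at each dose level, together with independence and counting increases. The joint cervical test uses the same women as its strata, so independence is impossible.
- **Section 9 need not have promoted the objective.** No text says its headings override the tables, and the merged list in section 4.1 suggests loose grouping. Nor is the verb demonstrate evidence of promotion, since the tables that say exploratory use it too. What stands is narrower: the labels conflict and nothing resolves them.
- **The one-of-ten rule is assumed.** No passage says one significant site is enough. Equally, none says what is needed, and the threshold in 9.1.3 is unqualified.
- **The tests may be fewer in practice.** With five evaluable pairs, the smallest two-sided Wilcoxon p-value is 2/2^5 = 0.0625, and section 4.2.1 expects productive anal samples to be scarce in cohort 1. If only the two cervical tests were usable, the independence ceiling would be 1 − 0.95² = 9.8% in either direction and 1 − 0.975² = 4.9% for reductions.
- **Multiplicity for lower-tier objectives is often left to a separate analysis plan.** That is fair, and a missing adjustment is not the complaint. The conflict lies inside the protocol, and a separate plan would inherit it.

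**Conclusion.** The concern holds as a contradiction about rank that changes what the trial may conclude. The 1-dose/2-dose objective is exploratory in two places, unresolved in a third and secondary in section 9. There it takes the primary analysis and an unqualified p<0.05, with no dependence on the 3-dose result.

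For 10 tests and no true effect, the chance of at least one false reduction is about 9% to 21%, against 2.5% for a single test. Counting either direction it is about 18% to 38%, against 5%. The error rate is uncontrolled and well above nominal, and the documents support nothing stronger than that.

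The figures rest on four assumptions: site correlations of 0.9 to 0, a shared Visit 1 baseline, all women compared at Visits 2 and 3, and any one significant reduction being read as a claim. The wording of 9.1.2.2.1 could instead mean only women who stopped after one or two doses. The count of ten tests would remain, but the correlations could differ. The partial analysis at half of recruitment (9.1.3) is not included.

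**What to change.** Use the exploratory label throughout:

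- In section 9, move Objective 3 out of 9.1.2 to its own tertiary/exploratory heading. In section 4.1, separate it from the antibody objective.
- Replace the verb demonstrate with explore for this objective in sections 1.1.5, 3, 4.1 and 9. Changing section 9 alone would create a new inconsistency.
- State that the p<0.05 rule of 9.1.3 supports no claim for this objective. Report the median before-after change with a 95% confidence interval for each dose level and site.
- Say in 9.1.2.2.1 which women and visits are meant.

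If the sponsor wants one formal reduced-dose claim, test it in cervical samples only, in fixed sequence: 3-dose, then 2-dose, then 1-dose. Each step is at two-sided 0.05 and is taken only if the one before succeeded. Because 9.1.1.2 plans joint and stratified cervical analyses, name the one that carries the sequence.

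The cost is wording in four sections, with no added samples or patients. The downside is that a lone nominal p<0.05 after one or two doses can no longer be reported as a demonstrated effect.
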